### Follow-up

At the end of the survey, participants will be able to opt-in to a possible future in-depth qualitative interview by providing their contact details (name, email address, phone number) to an email address that will be provided to them. This will allow the research team to explore topics identified from the quantitative data in more depth. Participants will also have the option of providing their personal details to receive an easy to understand summary of results (see ‘Dissemination of results’ below).

If participants do not provide their contact details through that route, no follow-up will occur with participants. Participants will not be contacted individually with results from this survey, however an easy-to-read summary of the results of the survey will be published on the WHO website. While this survey may not result in direct benefit to individuals enrolled, participants may appreciate the opportunity to share their experience regarding how cancer has impacted their health and their current life. We also anticipate this study will have broader public health benefits.

### Timeline and status

A pilot version of the survey was launched in October 2022, after obtaining Ethics approval and appropriate stakeholder feedback on the content and format of the questions. The pilot survey was launched in English, French and Spanish. The Steering Committee used pilot findings and stakeholder and participant feedback on the pilot survey to develop the final version of the survey. The final survey will be available in other languages too as mentioned above. To increase representation from people in LMIC and men, who were under-represented in the pilot sample, additional direct meetings and communication were undertaken with stakeholders from the Advisory Committee to improve dissemination and participant recruitment. We anticipate relaunching the survey in October 2023, completing data collection and beginning data analysis and synthesis in the first quarter of 2024.

## Data management and statistical analysis

### Data management and confidentiality

All data will be collected, securely stored, and managed confidentially and locally within WHO, via the LimeSurvey software [73]. Identifiable data will only be collected and stored from participants who request follow-up by sending an email to the study group. Personal data will be linked to a newly created personal ID number in a document stored on a secure WHO server with access permitted only by the study team. Follow-up with participants who have provided their details will be done by members of the study team only. All personal data will be destroyed 5 years after publication of results.

Study data will only be accessible to the research team and will not be shared with any other external organisation or individual during the data collection period. All data will be digital, and no hard copies will be stored. All data will be stored for a total of five years from publication, after which it will be destroyed.

### Data analysis

The survey results will be analysed quantitatively per respondent group (people affected by cancer, their families and carers), per time from diagnosis, as well as by disease and age group (e.g.: paediatric neuro-oncology, paediatric leukaemia) and by country.

Quantitative variables will be summarised using means and standard deviations or medians and interquartile ranges, as appropriate. Categorical variables will be summarised using frequencies and percentages. Summary statistics will be presented along with a 95% confidence interval, to reflect the uncertainty in their estimation.

The anticipated total sample size is 2000 respondents. Within a particular subgroup, a sample size of 300 independent responses would provide a 95% confidence interval for the mean of a quantitative variable with a margin of error of ± 0.11 standard deviations. For the proportion associated with a categorical response, the margin of error would be no larger than ± 6%. Where it is possible to identify non-independent groups of responses (e.g., participants recruited via snowball sampling), standard errors will account for the clustering.

It should be noted that the sampling approach will be subject to both selection and non-response biases, as some of the target population will not be aware of the questionnaire, and others will choose not to respond. In order to assist with interpretation, where possible, the basic demographic characteristics of respondents will be contrasted to those of the target population, and the characteristics of early versus late respondents will be compared [74].

Additional limitations to a cross-sectional design include the wide range of participants included in this study (age, different diseases, time since diagnosis, patients, caregivers and bereaved). Finally, the aim of this study is to describe the current situation of people with a lived cancer experience. This study will not attempt to derive causal relationships between a cancer diagnosis and participants’ current or past lived experience.

A detailed analysis plan will be prespecified prior to undertaking analyses to address more complex research questions, for example, to define regression models that explore the interrelationships between different survey variables.

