Participants will be anonymously recruited via convenience and snowball sampling through networks of organisations related to cancer. To date, the survey has been shared within the WHO and with partner networks of international cancer organisations via a webinar, direct meetings, as well as through direct emails to organisation leaders. Cancer organisations that were chosen to disseminate the survey focus on childhood and on adult cancer (including specific cancers such as women’s cancer), with a broad geographical representation. These include professional partner organisations, research institutes, as well as foundations and advocacy groups (S2 Table). Organisations will be permitted to advertise the survey on social media a maximum of three times. Physicians and other healthcare providers have not directly been approached to identify participants.

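### Clustered standard errors are promised, but no way to identify clusters in this anonymous snowball survey is described, so the reported 95% intervals may be too narrow

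*Protocol article*

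**What the plan says.** The Data analysis section of the protocol article attaches an interval to every summary: "Summary statistics will be presented along with a 95% confidence interval, to reflect the uncertainty in their estimation". Precision is stated for a subgroup: "a sample size of 300 independent responses would provide a 95% confidence interval for the mean of a quantitative variable". The half-width given for such a mean is ±0.11 SD. For a proportion, "the margin of error would be no larger than ± 6" percent. On the whole sample, "The anticipated total sample size is 2000 respondents".

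Non-independence is handled in one sentence: "Where it is possible to identify non-independent groups of responses (e.g., participants recruited via snowball sampling), standard errors will account for the clustering".

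Participants and recruitment says: "Participants will be anonymously recruited via convenience and snowball sampling through networks of organisations related to cancer". The Abstract also describes data collection as anonymous. Data management and confidentiality limits identifiable data to people who email the study group to ask for follow-up. Table 1, which the article calls a summary of the questionnaire, lists no item on how the link was received, who passed it on, or whether a relative has also answered. The comprehensive table (S1) is not among the documents at hand.

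**The concern.** The design makes dependence between responses likely. Recruitment runs through chosen organisations, their social media adverts and onward referral. Patients, spouses, children, siblings and other caregivers are all eligible, so one cancer case can produce several responses.

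The plan recognises this, but its safeguard works only for clusters that can be seen. Its one example, snowball recruits, is the kind of cluster that anonymous recruitment makes hardest to see unless a marker is collected on purpose. Where no cluster is identified, the rule makes no adjustment and the interval is computed as if responses were independent. With positive within-cluster correlation, such intervals are too narrow.

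The timing matters. A later analysis plan can choose an estimator, but it cannot recover a source variable that was never stored. The results are meant to feed a WHO practice brief with recommendations to Member States, so overstated precision could carry into policy documents.

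**Working it through.** **Inputs from the article (Data analysis):** n = 300 independent responses per subgroup; 95% two-sided confidence, so z = 1.96; margins of ±0.11 SD and no larger than ±6%; total of 2000.

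**Inputs not in the article (assumptions):** m, the number of responses per cluster within the analysed subgroup, and the intra-cluster correlation (ICC). I take ICC = 0.05 and m = 2, 10 and 30.

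**Step 1: the plan's own figures.**
- Mean: 1.96/√300 = 0.113 SD (stated ±0.11).
- Proportion, worst case p = 0.5: 1.96 × √(0.25/300) = 5.66 percentage points (stated no larger than ±6%).

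Both reproduce.

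**Step 2: formulas under clustering.**
- Design effect: DEFF = 1 + (m − 1) × ICC
- Effective sample size: 300/DEFF
- Correct margin: independent margin × √DEFF
- True coverage of an unadjusted 95% interval: 2Φ(1.96/√DEFF) − 1
- Responses needed to keep the stated margins: 300 × DEFF

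**Step 3: results at ICC = 0.05.**

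| m | DEFF | Effective n | Mean (SD) | Proportion | Unadjusted coverage | Responses needed |
|---|---|---|---|---|---|---|
| 2 | 1 + 1 × 0.05 = 1.05 | 286 | ±0.116 | ±5.8% | 94.4% | 315 |
| 10 | 1 + 9 × 0.05 = 1.45 | 207 | ±0.136 | ±6.8% | 89.6% | 435 |
| 30 | 1 + 29 × 0.05 = 2.45 | 122 | ±0.177 | ±8.9% | 79% | 735 |

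Coverage here concerns sampling error only; it leaves aside the selection bias that the article already admits.

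**Step 4: how much clustering breaks the ±6% bound.** Solve 1.96 × √(0.25 × DEFF/300) = 0.06, which gives DEFF ≈ 1.12. At ICC = 0.05 this lies between m = 3 (DEFF 1.10) and m = 4 (DEFF 1.15).

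**Step 5: family pairs.** If a fraction f of a subgroup consists of pairs with correlation ρ, then DEFF = 1 + fρ. With every respondent paired (f = 1) and ρ = 0.3 to 0.5, DEFF is 1.3 to 1.5. Results are analysed per respondent group, however, so a patient and a spouse fall in different groups and do not inflate the variance of either mean. Only same-group relatives count, such as two parents. With an assumed f = 0.2, DEFF is 1.06 to 1.10. Family clustering alone is therefore a small matter in group-specific summaries.

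**The case against.** The strongest reply is that the article has already dealt with this. It gives the margins expressly for independent responses, raises non-independence itself, and commits to clustered standard errors where clusters can be found. It admits selection and non-response bias and plans comparisons to help interpretation. The study is descriptive, with no test or decision rule that turns on interval width. The introductory questions in Table 1 are described only as forced-choice and purposely developed, and S1 is not shown, so a source item may exist. If the 2000 respondents split evenly over the four recruited groups, each would have 500, and the stated margins would hold up to DEFF = 500/300 = 1.67.

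Much of this stands. A reader might infer that anonymity makes the clustering correction impossible. The documents do not support that: an organisation-specific link or source question identifies no one, and country is already an analysis variable. A reader might also infer that ±0.11 SD and ±6% are wrong, or that the intervals are certain to be too narrow. The margins are right under their stated condition, and the size of any shortfall depends on two quantities the article does not give.

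Some of the reply does not stand. The admitted biases concern where the estimate lies, not the width of the interval, and the article nowhere warns that intervals may be too narrow. Country does not identify an organisation, referral chain or family, and within a by-country summary it is a single cluster. The even-split calculation does not help the analyses by disease, age group and country, where subgroups would be smaller. The later detailed plan is described for more complex questions such as regression, while the descriptive intervals and the clustering rule are set in this section.

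**Conclusion.** The point holds in a limited form. The article makes its clustering correction depend on identifying clusters, names snowball recruits as the example, and describes no means of identifying them in an anonymous survey. Its margins are correct for independent responses and are best-case for the responses this recruitment will yield.

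The consequence runs from negligible to material. At an assumed ICC of 0.05, unadjusted coverage is about 94% with clusters of 2, 90% with clusters of 10 and 79% with clusters of 30. These figures illustrate a range and do not predict the result. The conclusion also rests on the visible summary of the questionnaire and would fall away in large part if S1 already contains a source and family item.

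**What to change.** Unless the full questionnaire already does this, make these changes before the relaunch:

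1. Give each disseminating organisation and language its own survey link, and store the resulting non-identifying source code with each response. A forwarded link carries its code, so onward referrals stay grouped with their source.
2. Add two forced-choice questions: how the respondent received the link, and whether they or a family member have already answered this survey or the pilot.
3. Use cluster-robust standard errors by source code for the summaries. Do not cluster by country within by-country summaries.
4. Run a sensitivity analysis that excludes repeat and same-family responses.
5. In Data analysis, label the margins as best-case and add a range. For example, over design effects of 1.05 to 2.45, 300 actual responses give about ±0.12 to ±0.18 SD and ±6% to ±9%, or 315 to 735 responses are needed to keep the stated margins. Identify the ICC and cluster sizes behind the range as assumptions.
6. Add a sentence that intervals may be too narrow where clusters cannot be identified.

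The cost is a set of links, two extra questions and a less favourable stated precision. No personal data are collected. If data collection has already begun without a source code, items 5 and 6 can still be done, but clusters among responses already received may not be recoverable.

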## Outcomes and dissemination

### Study outcomes

Outcomes of this study will include a description of different aspects of the lived cancer experience, in HICs and LMICs (Table 2).

**Table 2 pone.0294492.t002:** Study outcomes.

A description of:
1. Immediate and long-term financial impact of cancer on people affected by cancer and their family members.
2. Physical health and quality of life of people affected cancer and their family members.
3. Emotional well-being, mental health, and psychological supports of people affected by cancer and their family members.
4. Social well-being (relationships, work, and education) of people affected by cancer and their family members.
5. The nature of information received by people affected by cancer and their family members, and the degree of satisfaction in relation to the information received.
6. Survivors’ and their family members’ perception of quality of cancer care during and after treatment.
7. Survivors’ opinions and experience accessing follow-up and survivorship multidisciplinary care.
8. Siblings’ experience of cancer.
9. Caregiving experience of family members/caregivers and the impact of caring for someone with cancer on family members/caregivers.
10. Bereaved family members’ experience of cancer.

### Implications for future research

Results from this study will allow WHO and the research team to provide a description of the lived experience of people affected by cancer globally, particularly focusing on their psychosocial and financial needs. This has the potential to contribute to the development of legislative and policy interventions for professionals and governments designed to support people living with cancer and their families, led by WHO. This study may also lead to subsequent research questions focusing on the needs of people affected by cancer and their family members and caregivers, in different nations.

### Dissemination of results and publication policy

A webinar will be conducted before the publication of the results. The objectives of the webinar will be to disseminate results to professional organisations, regional WHO offices, cancer organisations, grassroot organisations and to the Advisory Panel, to raise awareness and to commence translating the results into practical recommendations. Future implementation studies may allow us to monitor the implementation of these recommendations.

Results will also be disseminated through peer-reviewed publications and through presentations at appropriate conferences and seminars. A synthesis of the findings will allow WHO and the research team to create a WHO practice brief on the lived experience of people affected by cancer. The brief will provide practical recommendations for Member States and suggest possible international collaborations to meet those needs; setting the agenda for person-centred cancer care. This practice brief and recommendations will be available on the WHO website. An easy to understand summary of results will be shared with participants who wish to receive this via email (see ‘Follow-up’ section).
